## Abstract

**Background:**

Surgical site infection (SSI) represents a major burden for patients, doctors, and health systems around the world. The aim of this trial is to assess whether the practice of using separate sterile gloves and instruments to close wounds at the end of surgery compared to current routine hospital practice can reduce surgical site infection at 30-days post-surgery for patients undergoing clean-contaminated, contaminated, or dirty abdominal surgery.

**Methods:**

This study protocol describes a pragmatic, international, multi-centre, 2-arm, cluster randomised controlled trial, with an internal pilot. Clusters are defined as hospitals within low- and middle-income countries (LMICs) defined by the Development Assistance Committee (DAC) Official Development Assistance (ODA) list, where there are at least 4 eligible hospitals per country. Hospitals (clusters) must be in LMICs where glove and instrument change are not currently routine practice. Patients (adults and children) undergoing emergency or elective abdominal surgery for a clean-contaminated, contaminated, or dirty operation are eligible for inclusion. Before closing the abdominal wall, surgeons and the scrub nurse will change gloves and use separate, sterile instruments (intervention), versus no changing gloves or using separate, sterile instruments (standard practice, control). The primary outcome is SSI within 30 days after surgery, using the Centre for Disease Control (CDC) criteria. Secondary outcomes are SSI before point of hospital discharge, and readmission, reoperation, length of hospital stay, return to normal activities, and death up to 30-days after surgery. A 12-month internal pilot, including 12 clusters and approximately 600 participants, aims to assess adherence to allocation and follow-up of patients. The main trial is powered to detect a minimum reduction in the primary outcome from 16 to 12%. A total of 12,800 participants will be recruited from 64 clusters (hospitals) each including at least 200 participants.

**Discussion:**

Change of gloves and sterile instruments prior to fascial closure in abdominal surgery is a low-cost, simple, intraoperative intervention which involves all members of the surgical and scrub team. If effective at reducing SSI, this practice could be readily implemented across all contexts. The findings of this trial will inform future guideline updates from international healthcare organisations, including the World Health Organization.

**Trial registration:**

ClinicalTrials.gov NCT03980652. Registered on 9 July 2019

**Supplementary Information:**

The online version contains supplementary material available at 10.1186/s13063-022-06102-5.

## Administrative information

Note: the numbers in curly brackets in this protocol refer to SPIRIT checklist item numbers. The order of the items has been modified to group similar items (see http://www.equator-network.org/reporting-guidelines/spirit-2013-statement-defining-standard-protocol-items-for-clinical-trials/).

## Introduction

### Background and rationale {6a}

#### Background

Surgical site infection (SSI) represents a major burden for patients, doctors, and health systems around the world but is potentially preventable. SSI is the commonest postoperative complication across all income and development settings, and the commonest healthcare-associated infection in low- and middle-income countries (LMICs) [1, 2]. It has been associated with one third of postoperative deaths and accounts for 8% of all deaths caused by a nosocomial infection [3]. Rates vary significantly between different types of surgery, but it is particularly prevalent in abdominal operations with as many as one in four patients having an SSI when the operation involves the bowel [4]. SSIs cause pain and discomfort, increasing the time taken to return to work and other normal activities [5]; in resource-limited settings, this is disproportionately high since personal income is less and patients are required to pay for their own treatment [6]. The GlobalSurg-2 cohort study captured the incidence of SSI in these patients, demonstrating how it affects people around the world and how those in the poorest setting are at greatest risk [7, 8]. Whilst there are no direct data on the costs of SSI in LMICs, the burden of increased healthcare costs on patients, communities, and providers in low-income settings is likely to be substantial. Reducing SSI has an important impact on patients around the world.

#### Rationale

Improving surgical outcomes is a global health priority, highlighted by the Lancet Commission on Global Surgery [9]. Recent World Health Organization (WHO) guidelines made 29 recommendations for measures to prevent SSI, but there was little high-quality evidence to support most of these interventions [10, 11]. A Delphi consensus was undertaken by an international panel of surgeons to identify the WHO recommendations in greatest need of better supporting evidence [12]. The WHO recommendations for change of gloves and sterile instruments at the time of fascial closure were identified as the priority recommendations.

Specific evidence for SSI reduction with glove and instrument change before fascial closure is limited, including only small RCTs at high risk of bias; three studies have been published to date, all suggesting a benefit. The largest RCT (*n* = 182) included patients undergoing pancreatic surgery in a single Japanese hospital, finding a significantly lower SSI rates in the intervention group (2.2% v 12.4%, *p* = 0.002) [13]. Of the two other RCTs, the first (*n* = 92) demonstrated a reduction in the risk of SSI after vascular surgery (5.0%) versus 12.5%, *p* < 0.02) [14, 15]. These early clinical data support the need for a major, pragmatic multicentre trial in LMICs where the burden of complications is greatest.

Due to the heterogeneous evidence base, CDC, WHO, and NICE guidelines do not make recommendations on the practice of change of gloves/instruments as part of routine care. The executive summary of the 2017 WHO Guidelines on SSI reduction practice states: As there is no direct evidence of the effectiveness of sterile surgical instruments to wound closure, well-designed RCTs would be welcome. Studies should be conducted in high-, low-, and middle-income countries and include different surgical procedures using an SSI outcome defined according to CDC criteria [16].

### Objectives {7}

The aims and objectives for the pilot and the main trial are set out separately.

#### Internal pilot

The aim of the 12-month internal pilot is to assess (1) whether hospitals adhere to their allocation and (2) what proportion of patients who are eligible for ChEETAh can be followed up successfully at 30 days after their surgery.

STOP-GO criteria will be assessed at 12 months following the commencement of recruitment. A traffic light system will be used to determine feasibility of progression to the main trial:
Green: ⩾ 80% intervention adherence in patients eligible for ChEETAh; ⩾80% of eligible patients followed up. If both criteria are met, the study will continue unchanged.Amber: 50–79% intervention adherence; 50–79% followed up. If at least one amber criteria is met, the study will need review to see what changes (if any) could be made for improvement.Red: < 50% intervention adherence; < 50% followed-up. If one or both of these criteria are met we will discuss the feasibility of the trial continuing with the Trial Steering Committee.

#### Main trial

The primary objective is to assess whether the practice of using separate, sterile gloves, and instruments to close wounds at the end of surgery can reduce surgical site infection at 30-days post-surgery for patients undergoing clean-contaminated, contaminated, or dirty abdominal surgery, compared to current routine hospital practice.

The secondary objectives are to assess the impact of changing gloves/instruments prior to wound closure compared to current routine hospital practice on secondary clinical outcomes up to 30 days post-surgery including: SSI during the in-hospital stay, re-admission, re-operation, length of hospital stay, return to normal activities, and death.

### Trial design {8}

CHEETAH is an international, multicentre, 2-arm, cluster randomised controlled trial with an internal pilot, to evaluate the use of separate sterile gloves and instruments at the time of wound closure to reduce SSI rates in patients undergoing surgery with an abdominal incision. Clusters are defined as hospitals. Clusters will be randomly allocated (1:1) to change of gloves and instruments (intervention group) or current routine hospital practice (Fig. 1). Randomisation will be minimised by country (minimum participating of four clusters per country in order to achieve balance by treatment arm) and hospital type (referral hospital (yes or no) where a referral hospital is defined as a hospital that accepts pre-operative referrals from other surgical teams).

**Fig. 1 Fig1:**
[figure not shown]
Trial schema

## Methods: participants, interventions, and outcomes

### Study setting {9}

This protocol has been reported in compliance with the Standard Protocol Items: Recommendations for Interventional Trials (SPIRIT) guideline [17].

Eligible hospitals (clusters) are any LMIC hospital performing abdominal surgery where glove and instrument change is not currently routine practice. LMICs are defined by the Development Assistance Committee (DAC) Official Development Assistance (ODA) list where there are at least 4 eligible hospitals per country. Participating sites are planned for inclusion from seven LMICs in total including (alphabetically) Benin, Ghana, India, Mexico, Nigeria, Rwanda, and South Africa.

### Eligibility criteria {10}

In clean (non-contaminated) surgery, the infection rate is low and benefits from research into interventions targeting SSI rates in those patients are limited. CHEETAH will therefore focus on clean-contaminated, contaminated, and dirty surgery.

Patients (adults and children) undergoing emergency or elective abdominal surgery for any indication (including trauma), with an intra-operative finding of clean-contaminated, contaminated, or dirty operation with at least one abdominal incision of 5 cm or greater are eligible for inclusion. Patients undergoing caesarean section will be excluded, as in many sites in LMICs, there is a risk they dominate recruitment and prevent a representative case-mix for other types of abdominal surgery. CHEETAH has no defined age limits, but each participating country will define age criteria based on country-specific regulatory approval processes.

Each participating hospital will develop a local pathway to recruit eligible patients. Potentially eligible patients can be identified by any member of the surgical team (research nurse, clinical officer, surgeon in training, operating surgeon), either before, during, or after surgery but before discharge.

### Who will take informed consent? {26a}

Individual patient-level consent for exposure to the intervention or routine hospital practice is not possible since the randomisation is at the hospital level. Hospitals randomised to the intervention are likely to change practice for all patients once randomised.

All patients undergoing abdominal surgery and who satisfy the eligibility criteria will be followed up at 30-days post-surgery. Consent for data collection in the context of the CHEETAH trial protocol will be for data collection only and will be sought at the 30-days post-surgery follow-up time point. Other data collected is collected as part of normal practice.

For patients returning as part of routine care at 30-days, written consent will be sought for the collection of the 30-day follow-up data. A patient information sheet (PIS) (see Appendix 1) will be provided to those patients providing written informed consent (see Appendix 2), following which patients are asked to give informed consent to participate in the trial. The PIS has been translated into appropriate languages as advised by local research ethics committees.

Those patients that do not return to hospital as part of standard care, will be contacted by telephone, and will be asked to provide explicit verbal consent during the call for the collection of trial-related data at 30 days, and this will be clearly documented on the CHEETAH 30-day follow-up case report form (CRF) (see Appendix 3_CHEEATH Adult CRF 30 day Follow-up_verbal consent). The consent process will be agreed by each Country Lead investigator according to relevant national guidelines and in line with country-specific regulatory board requirements.

### Additional consent provisions for collection and use of participant data and biological specimens {26b}

This trial does not involve collecting biological specimens for storage.

### Interventions

#### Explanation for the choice of comparators {6b}

The comparator is current routine hospital practice (no change of gloves or use of separate, sterile instruments *before* closing the abdominal wall).

#### Intervention description {11a}

The intervention used within CHEETAH is change of gloves and use of separate, sterile instruments before closing the abdominal wall.

In sites randomised to the intervention group, since the final level of contamination may not be known until during the operation, all cases need to be prepared for glove and instrument change, if required. Clean instruments should be set to one side if using instruments from the main tray (e.g. needle holder, forceps, suture scissor tied in a swab). If using instruments from a new pack, these should be available in the operating theatre but unopened. When to change gloves and use clean instruments: change of gloves and instruments should be undertaken for all clean-contaminated, contaminated, and dirty surgeries. After completion of the abdominal component of the operation and at the time of the count of surgical swabs and instruments (preparing for the ‘sign out’ component of the WHO Surgical Safety Checklist [18]), the surgical team should confirm eligibility of the participant.

If the patient is eligible, the surgical team should change gloves and use the clean instruments before handling the wound edges to facilitate closure. This includes two key components: (1) gloves: change of sterile gloves (or outer gloves if double gloved) for operating surgeon, assistant surgeon(s), and scrub staff (2); instruments: a sterile set of instruments should be used for abdominal wall closure including a needle holder, forceps, and scissors. This should be implemented in each hospital according to local practice and availability. For example, they can be separated from the main instruments at the start of the operation by the scrub nurse (e.g. wrapped in a clean swab). Alternatively, a new instrument(s) pack may need to be opened.

Through site surveys to address trial feasibility, most hospitals do not require additional instrument packs. Where required, Birmingham Clinical Trials Unit will work with Hubs to provide this, where feasible. The additional gloves required for the trial will be funded as part of the hospital’s normal glove purchasing processes (and then reimbursed via the Hub), to provide efficiencies in terms of supply and stock. The ICC/BCTU and the Hubs will request a report from individual hospitals for accountability of interventions.

#### Criteria for discontinuing or modifying allocated interventions {11b}

On occasion, changing gloves or instruments will occur (e.g. surgeon preference), and this will be recorded in the intraoperative CRF (see Appendix 4_Adult CRF booklet_Baseline & Intraoperative Form). Practice will be monitored throughout the trial to ensure adherence to the hospital’s allocation.

#### Strategies to improve adherence to interventions {11c}

Staff at participating hospitals (Hub or Spoke) will undergo a standardised site set-up training package. This will include (1) Online Good Clinical Practice, (2) online training modules (set-up, delivery, intervention, follow-up), (3) site initiation visit: from either BCTU or local Hub, and (4) a short ChEETAh ‘training phase’ to allow centres to adjust to change clinical practice for the delivery of the interventions. Intervention adherence will be monitored locally and centrally using the in-theatre CHEETAH Register, with the use of sterile gloves and instruments before fascial closure recorded for every case in a participating centre (see Appendix 5).

#### Relevant concomitant care permitted or prohibited during the trial {11d}

All other aspects of the operation, apart from those allocated as part of the trial intervention, will be determined by the attending surgeon and anaesthetist. Participating hospitals will implement the World Health Organization Surgical Safety Checklist [18] for all participants to standardise perioperative care prior to site opening [18]. The individual components will not be enforced.

Within this pragmatic trial, other SSI reduction measures may be used at the surgeon’s discretion (skin preparation solution, wound edge protector, triclosan sutures, wound washout, negative pressure wound therapy).

#### Provisions for post-trial care {30}

The University of Birmingham has in place Clinical Trials indemnity coverage for this trial which provides cover to the University for harm which comes about through the University’s, or its staff’s, negligence in relation to the design or management of the trial. The risk of the trial is no greater than the risk of the standard clinical care. Responsibility for the participants at sites remains with the organisation responsible for the clinical site, and it is therefore indemnified through their normal arrangements.

#### Outcomes {12}

The primary outcome is SSI up to 30-days after surgery (with the day of surgery as day 0) using the US Center for Disease Control (CDC) definition of deep incisional or superficial incisional SSI as follows:
The infection must occur within 30-days of the index operation;The infection must involve the skin, subcutaneous, muscular or fascial layers of the incision;The patient must have at least one of the following: purulent drainage from the wound; organisms detected by wound swab; diagnosis clinically or at imaging; wound opened spontaneously or by a clinician;The patient has at least one of the following: pain, tenderness, localised swelling, redness, heat at the wound site, systemic fever (> 38 °C).

The secondary outcomes are:
SSI at discharge from hospital, based on the CDC definition;Unexpected re-admission into hospital for a wound-related problem within 30-days post-surgery;Unexpected re-operation for a wound-related problem within 30 days post-surgery;Length of hospital stay (index hospital admission);Return to normal activities within 30 days of surgery;Death within 30 days of surgery

#### Participant timeline {13}

Prior to registration, final eligibility for entry into the ChEETAh trial must be confirmed. This can only be performed after the operation when the *actual* length of incision and *actual* contamination level at the time of surgery is known.

Once eligibility has been confirmed, patients will be registered by a member of the hospital-based research team. The next sheet of ChEETAh trial number stickers located in the ChEETAh Trial Investigator Site File (ISF) should be selected, along with a ChEETAh CRF booklet. The CRF booklet will capture baseline details, operative details, and SSI information at discharge (Fig. 2).

**Fig. 2 Fig2:**
[figure not shown]
CHEETAH patient inclusion pathway

The ChEETAh trial number stickers should be affixed to the first page of the CRF booklet and all subsequent CRF pages in the spaces provided, i.e. in the box with the text ‘Please affix sticker here’. This unique trial number will be used in all correspondence between the Hub, spoke, and BCTU and will help identify patients registered in the ChEETAh trial.

The patients trial number should be recorded on the ChEETAh Trial Register and the patient should be registered on the trial database by logging on to the ChEETAh database (https://bctu-redcap.bham.ac.uk/).

Patients will be reviewed, at the time of discharge from hospital, and at post-operative day 30. If a patient achieves the primary outcome before 30 days, they should still be assessed at 30 days to record secondary outcome measures.

Once registered into the ChEETAh trial, the patient will be contacted on or after, but as close as possible to postoperative day 30 by a member of the research team (from the Hub or Spoke) to complete the 30-day follow-up assessment.

Follow-up will be completed in-person for those returning to hospital as part of standard, routine care; all other patients will be followed up by telephone 30-days post-surgery (Table 1).

**Table 1 Tab1:** Participant timeline and schedule of assessments

Process	Trial document	Intraoperative	Trial entry	Discharge	30-day follow-up
Identify potential patients					
Operation	ChEETAh sticker for inclusion in operation notes)	X			
Initial eligibility check	ChEETAh register	X			
Final eligibility Check	CRF booklet ➢ Intraoperative form ➢ Patient contact form		X		
Adherence to allocated interventions	CRF booklet ➢ Intraoperative form		X		
Assessment for SSI	Follow-up form			X	X

### Sample size {14}

#### Internal pilot

Twelve centres with an average of 50 patients each during a staggered opening will result in at least 600 patients. The stop-go criteria indicates that for green light, ⩾ 80% intervention adherence in patients eligible for ChEETAh is expected (95% CI: 77% to 83%) and ⩾ 80% of eligible patients should have been followed up (95% CI: 77% to 83%). For amber light, 50–79% intervention adherence in patients eligible for ChEETAh is expected and 50–79% of eligible patients should have been followed up. For red light, < 50% intervention adherence in patients eligible for ChEETAh is expected (95% CI: 46% to 54%) and < 50% of eligible patients should have been followed up (95% CI: 46% to 54%).

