## Statistical methods

### Statistical methods for primary and secondary outcomes {20a}

#### Internal pilot

Percentages of subjects that adhered to allocation and subjects that were followed up will be presented alongside 95% confidence intervals. The percentages will be presented for all centres combined and for each centre separately.

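### The pilot's 95% intervals (77–83% and 46–54%) ignore clustering within the 12 hospitals, so the stated precision is somewhat too good

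*Protocol article*

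**What the plan says.** In Sample size {14}, Internal pilot, the protocol article sets the pilot size as follows: "Twelve centres with an average of 50 patients each during a staggered opening will result in at least 600 patients". This same paragraph attaches a 95% interval to two of the three traffic-light levels.

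- Green, at 80%: for adherence "intervention adherence in patients eligible for ChEETAh is expected (95% CI: 77% to 83" per cent, and for follow-up "of eligible patients should have been followed up (95% CI: 77% to 83" per cent.
- Red, at 50%: for adherence "intervention adherence in patients eligible for ChEETAh is expected (95% CI: 46% to 54" per cent, and for follow-up "of eligible patients should have been followed up (95% CI: 46% to 54" per cent.

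The paragraph mentions no clustering, intra-class correlation or design effect. Yet Trial design {8} states "Clusters are defined as hospitals", and the first pilot aim in Objectives {7} is to find out "whether hospitals adhere to their allocation".

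The next paragraph (Sample size {14}, Main trial) inflates the main-trial sample by 1 + (n − 1)ρ. It reports an intra-class correlation of 0.02 from feasibility data, assumes 0.01, and allows for a coefficient of variation of cluster size of 0.5.

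For the pilot analysis, Statistical methods {20a} says: "Percentages of subjects that adhered to allocation and subjects that were followed up will be presented alongside 95% confidence intervals". These are to be given pooled over hospitals and for each hospital. No interval method is named.

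**The concern.** Whether gloves and instruments are changed, and whether a patient is reached at 30 days, depends largely on how a hospital and its research team work. Patients of one hospital therefore tend to share these outcomes. Any positive correlation within hospitals makes an interval based on 600 independent patients too narrow.

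The printed intervals are the only quantitative support the paragraph offers for the pilot size. They tell the reader that 12 hospitals fix adherence and follow-up to within 3 or 4 percentage points. If that is optimistic, a result near 80% or near 50% will look firmer than it is when the trial team reviews possible changes (amber) or discusses feasibility with the Trial Steering Committee (red). The paragraph also departs from the treatment of clustering that the same section applies to the main trial.

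**Working it through.** **Inputs.** 12 hospitals averaging 50 patients, n = 600; thresholds p = 0.80 and p = 0.50 (Sample size {14}, Internal pilot). Intra-class correlation (ICC) 0.01 and 0.02, and coefficient of variation of cluster size 0.5 (Sample size {14}, Main trial). ICCs of 0.05 and 0.10 are assumptions of this review.

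**Step 1: reproduce the printed figures.** Half-width = 1.96 × √(p(1 − p)/600).

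- p = 0.80: 1.96 × √(0.16/600) = 1.96 × 0.01633 = 3.2 points, giving 76.8–83.2% (printed 77–83%).
- p = 0.50: 1.96 × √(0.25/600) = 1.96 × 0.02041 = 4.0 points, giving 46.0–54.0% (printed 46–54%).

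Both match after rounding with a design effect of exactly 1.

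**Step 2: apply the protocol's own design effect.** With equal clusters of 50, DE = 1 + 49 × ICC, and each half-width is multiplied by √DE.

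| ICC | DE | 600/DE | Around 80% | Around 50% |
|---|---|---|---|---|
| 0 (as printed) | 1.00 | 600 | 76.8–83.2% | 46.0–54.0% |
| 0.01 (protocol, SSI) | 1.49 | 403 | 76.1–83.9% | 45.1–54.9% |
| 0.02 (protocol, SSI) | 1.98 | 303 | 75.5–84.5% | 44.4–55.6% |
| 0.05 (assumed) | 3.45 | 174 | 74.1–85.9% | 42.6–57.4% |
| 0.10 (assumed) | 5.90 | 102 | 72.2–87.8% | 40.3–59.7% |

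At the protocol's ICCs the half-width grows by a factor of √1.49 = 1.22 to √1.98 = 1.41.

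**Step 3: refinements.** With only 12 clusters, a t quantile on 11 degrees of freedom is the more natural multiplier. At ICC 0.02 it gives 74.9–85.1% and 43.7–56.3%. With the main trial's coefficient of variation of 0.5 and the normal quantile, DE = 1 + (1.25 × 50 − 1) × ICC. That gives 75.9–84.1% and 44.9–55.1% at ICC 0.01 (DE 1.615), and 75.2–84.8% and 44.0–56.0% at ICC 0.02 (DE 2.23).

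**Step 4: how small must the ICC be for the printed figures to stand?** The rounded interval at 80% survives while the half-width stays below 3.5 points: DE < (3.5/3.2)² ≈ 1.196, so ICC < 0.196/49 ≈ 0.004. At 50% the limit is 4.5 points: DE < (4.5/4.0)² ≈ 1.266, so ICC < 0.266/49 ≈ 0.0054. Both limits lie below the 0.01 that the protocol assumes for the main trial.

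**The case against.** The strongest reply is that nothing depends on these intervals. The traffic-light rules in Objectives {7} compare observed percentages with 80% and 50%; no rule uses an interval bound. Every pilot result gets the same colour whichever interval is printed. The pilot size is not derived from a precision target, and the main-trial sample size is untouched. All of this stands.

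The size of the effect is also limited. At the protocol's own ICCs each bound moves by about 0.7 to 1.6 points. The wider intervals rest on ICCs that the protocol does not give. It is plausible that adherence to a hospital policy clusters more strongly than SSI, but the document does not show it. This stands too: the direction is certain for any positive ICC, the size is not.

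A reader might infer that the 12-hospital pilot cannot tell green from amber at all. The document does not support that. At ICC 0.01 (effective n = 600/1.49 ≈ 403), an observed 85% has half-width 1.96 × √(0.1275/403) = 3.5 points and an observed 75% has 1.96 × √(0.1875/403) = 4.2 points; both intervals exclude 80%. At an assumed ICC of 0.10 (effective n ≈ 102), 85% has half-width 1.96 × √(0.1275/102) = 6.9 points and is no longer separated from 80%. Very close to 80%, even 600 independent patients could not decide the matter.

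A reader might also infer that the Trial Steering Committee would act on false precision at every level. Objectives {7} names that committee only for red, and there for a discussion of feasibility.

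Nor does Statistical methods {20a} commit to a wrong method. It names none, that detail may sit in a separate analysis plan, and the hospital-by-hospital percentages will show the spread directly. The demonstrated error is confined to the planning figures.

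**Conclusion.** The point holds as a statement about precision. The intervals are computed correctly for independent patients, but independence does not fit a pilot of 12 hospitals or the clustering adjustment made in the next paragraph. The intervals are too narrow for any positive correlation within hospitals. At the protocol's ICCs of 0.01 to 0.02 the understatement is modest: half-widths of 3.9 to 4.5 points instead of 3.2 at 80%, and 4.9 to 5.6 instead of 4.0 at 50%. At an assumed ICC of 0.05 to 0.10 they are 5.9 to 7.8 and 7.4 to 9.7 points.

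These figures assume clusters of 50 and carry ICCs from the SSI calculation over to adherence and follow-up, for which no value is given. The pilot separates green from amber, and amber from red, less precisely than stated; the stop-go rules and the main-trial design are unaffected.

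**What to change.** In Sample size {14}, Internal pilot, replace the printed intervals with cluster-adjusted ones, using DE = 1 + 49 × ICC over a stated range of ICCs for adherence and follow-up. The range should include at least 0.01 and 0.02 and some larger values marked as assumptions.

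For the pilot analysis, add one sentence, in Statistical methods {20a} or in the analysis plan if it is not already there. It should say that the pooled 95% intervals allow for clustering by hospital, for example from hospital-level proportions with a t quantile on the number of hospitals minus 1, or from cluster-robust standard errors.

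The cost is a few restated numbers and one sentence. The only downside is a less favourable stated precision.
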